## Abstract

“Nonspecific shoulder pain” encompasses various non-traumatic musculoskeletal shoulder disorders, diverging from diagnostic terminologies that refer to precise tissue-oriented clinical diagnosis. Blood flow restriction (BFR) training, involving partial arterial inflow and complete venous outflow restriction, has exhibited acute hypoalgesic effects primarily in healthy populations by increasing their pain thresholds. This study aims to examine whether a single BFR session with low-load exercises can alleviate pain perception among nonspecific shoulder pain patients. Conducted as a single-blind crossover randomised clinical trial, 48 adults (age range: 18 to 40) presenting with nonspecific shoulder pain will partake in two trial sessions. Random assignment will place participants into BFR or sham BFR groups and ask them to perform one exercise with BFR. Subsequently, participants will complete a shoulder girdle loading regimen comprising six exercises. The second session will involve participants switching treatment groups. Pain pressure thresholds (PPTs), shoulder pain and disability via the shoulder pain and disability index (SPADI), maximal voluntary isometric contraction (MVIC) of shoulder external rotators, pain during active abduction, and peak pain during shoulder external rotation will be evaluated using the numeric pain rating scale (NPRS). Immediate post-exercise assessments will include patient-perceived pain changes using the global rating of change scale (GROC) and participant-rated perceived exertion (RPE), employing a modified Borg’s scale (Borg CR10) post-BFR or sham BFR exercise session. Each session will encompass three assessment periods, and a combination of mixed-effect models and descriptive statistics will underpin the analysis. This protocol was approved by Cyprus National Bioethics Committee (ΕΕΒΚ/2023/48), and was registered in ClinicalTrials.gov (Registration number: NCT05956288). Conclusion: The anticipated outcomes of this study illuminated the acute effects of BFR training on pain perception within the context of nonspecific shoulder pain, potentially advancing strategies for managing pain intensity using BFR techniques.

## 1. Introduction

Shoulder pathologies are the third most common musculoskeletal condition encountered by health professionals in their day-to-day clinical practice, followed by low back and neck pain [1]. Notably, approximately 40–54% of patients report ongoing pain lasting 1–3 years [1], causing a significant economic burden on national healthcare systems and patients [2,3]. The pathologies associated with the development of shoulder pain are numerous; however, contemporary musculoskeletal shoulder pain research has emphasised the need to break free from diagnostic terminologies that refer to precise tissue-oriented clinical diagnosis [4]. The low validity and diagnostic accuracy of the special tests available to the clinician for shoulder joint evaluation [5,6,7,8] indicate the specific diagnosis as an elusive goal in clinical practice. In addition, the need to detach from diagnostic labels becomes even more intense if one takes into account the inability to correlate symptoms and clinical status with pathological findings in diagnostic tests [9,10,11]. Hence, for clinical practice, nonspecific shoulder pain is the preferred term as an umbrella term that includes non-traumatic musculoskeletal disorders of the shoulder.

Therapeutic exercise loading is the mainstay of conservative treatment and appears to be a powerful tool in the hands of clinicians to improve pain, mobility, and shoulder function in individuals with nonspecific shoulder pain [12]. Several mechanisms are thought to explain the benefits of exercise in nonspecific shoulder pain [13]. The most frequently mentioned neuromuscular mechanism suggests that strengthening the rotator cuff muscles inhibits pain [14]. Other mechanisms proposed are tissue factors (e.g., tendon remodelling, blood flow improvement, etc.), neuro-endocrine immunity (e.g., exercise-induced hypoalgesia, central and peripheral nervous system adaptations, etc.), and physiological mechanisms (e.g., improvements in self-efficacy and coping with pain, etc.) [13,15].

Blood flow restriction training (BFR) is a type of exercise with parallel partial restriction of the arterial inflow and complete venous outflow restriction in the muscle tissue that is usually combined with parallel execution of low-load resistance exercise loading. Blood flow restriction is achieved by using inflatable cuffs applied to both the upper and lower extremities [16,17]. During the last decade, the popularity of this technique seems to have grown rapidly due to its beneficial effects on increasing muscle strength and muscle hypertrophy in healthy adults [18,19,20] and clinical populations [21,22], as well as its acute hypoalgesic effect on the healthy population by significantly increasing the patient pain threshold [23,24,25]. However, to date, only one published study has examined the acute hypoalgesic effect of BFR training in a clinical population, showing beneficial adaptations in reducing pain in people with patellofemoral pain [26].

The primary objective of the present study is to evaluate whether a combination of a single acute BFR with a low-load exercise bout would reduce pain perception in patients with nonspecific shoulder pain and whether the potential hypoalgesia would be maintained after a 45 min physical therapy shoulder exercise loading session. The BFR exercise protocol will be compared to a sham BFR exercise protocol. We hypothesise that the participants in the BFR group would experience reduced pain perception and would be able to complete a scapula and rotator cuff muscle loading program with reduced pain.

## 2. Materials and Methods

### 2.1. Study Design

This crossover design randomised controlled clinical trial will include two intervention arms (BFR and sham BFR) with three assessment time points (baseline, immediately after BFR training, and at the end of the shoulder girdle exercise loading session) (Figure 1). Outcome measures assessment during the first (DAY 1) and the second session (DAY 2) will be performed by a blinded independent assessor to the intervention (sham BFR or BFR) to avoid the risk of “data collection ascertainment bias”.

All participants will be blinded to the group allocation to avoid the risk of “expectation bias” and “patient ascertainment bias” [27]. To achieve this, they will be informed that the effect of two different BFR occlusion protocols on pain perception after a low-load resistance exercise bout will be evaluated. The physiotherapists performing the interventions (BFR or Sham BFR) will not be blinded; however, they will not participate in the outcome assessment and will be blinded to the recorded values.

All participants will have an introductory baseline assessment. They will be asked to fill out questionnaires on sociodemographic characteristics, symptoms, comorbidities, and functional limitations. Subsequently, measurement of pain pressure thresholds (PPTs), administration of the Shoulder Pain and Disability Index (SPADI), measurement of maximal voluntary isometric contraction (MVIC), assessment of pain during active abduction, and maximal pain in shoulder external rotation on the numeric pain rating scale (NPRS) will be recorded. Then, participants will be randomly allocated to one of the two intervention groups (BFR and Sham BFR) and will be asked to perform one exercise with BFR. Immediately after the BFR session, they will be asked to evaluate the level of difficulty or exertion experienced during the BFR or Sham BFR exercise using the Borg CR1O scale [28]. Simultaneously, measurement of PPTs, MVIC, and maximal pain during external rotation, pain during active shoulder abduction, and perception of improvement or worsening of symptoms will be recorded. Finally, the participants will be asked to perform the shoulder girdle loading protocol, and a final assessment of the same outcome measures will be performed.

The participants will be crossover randomised, and the testing sessions will be at least 72 h apart to ensure that their clinical status (pain and other symptoms) has not changed. More specifically, they will be asked: “Has your clinical situation changed since last time?” If their answer is no, they will continue with the rest of the procedure; otherwise, they will be excluded from the second session, and this will be reported. This RCT is registered in ClinicalTrials.gov (Registration number: NCT05956288), and the study was designed according to the Consolidated Standards of Reporting Trials (CONSORT) guidelines for randomised clinical trials [29].

### 2.2. Sampling Method

Participants will be recruited through advertisements at local universities, physical therapy clinics, hospitals, and social media.

### 2.3. Participants and Sample Size

Adults presenting with nonspecific shoulder pain will be recruited using the following inclusion criteria: (1) age from 18 to 40 years, considering that the prevalence of degenerative rotator cuff tendinopathy increases from the age of 40 and above [30], (2) shoulder pain intensity greater than 4/10 on the NPRS [24] when performing active glenohumeral abduction and/or isometric resistance to glenohumeral external rotation at 0° of abduction, and (3) duration of symptoms greater than 3 weeks (to avoid an inflammatory component in the symptoms).

Participants will be excluded if they present any of the following criteria: (1) positive drop arm test (important indication for rotator cuff tear) [31], (2) cervical radiculopathy by presenting a positive specific Spurling test or neurological symptoms in the upper limb [32], (3) passive deficit in the active range of motion (AROM) at more than two levels of motion, where according to the literature it is an indication of a frozen shoulder [33], (4) body mass index (BMI) ≥ 30 [34], (5) previous shoulder surgery, (6) previous humerus fracture, (7) cancer, (8) rheumatic diseases, (9) systemic pathologies (e.g., diabetes, rheumatic disorder, fibromyalgia), (10) history of previous neurological disease, (11) history of thrombosis, (12) cardiovascular pathology, (13) neurological disease, (14) long-term use of corticosteroids, (15) injury to or surgery in the shoulder girdle less than 1 month from recruitment, (16) hypertension (systolic blood pressure greater than 140 mmHg and diastolic blood pressure greater than 90 mmHg), (17) anti-inflammatory drug treatment in the last 2 weeks, (18) injectable therapy (last 3 months), (19) previous experience/knowledge of BFR training [35], and (20) inability to write and read Greek.

The primary outcome used to calculate the required sample size using G* Power (v 3.1) software was pain. The sample size calculation was based on a previous study that reported an effect size of d = 0.6 for differences in the NPRS between groups after the BFR exercise [26]. To achieve 95% power at an alpha level of 0.05, 20 patients per intervention for 3 assessment periods of outcome measures are required. Given the crossover design of the study and the possibility that the status of the participants will change between the first and the second intervention, it is estimated that there will be a dropout of 20%, and thus, it is proposed to recruit 24 participants per group into the study, or 48 participants in total.

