#### 2.5.2. BFR Protocol

The vascular occlusion pressure needed for the complete occlusion of the upper extremity blood flow will be measured at rest, with the participant relaxed in the standing position [38], by placing a 6 cm wide and 60 cm long cuff on the more proximal part of the affected upper limb using an automatic personalised tourniquet system designed to automatically calculate limb occlusion pressure (MAD-UP Pro system, Angers, France) with clinically acceptable accuracy and high reliability [39,40]. Both intervention groups will perform the same exercise protocol. The limb occlusion pressure will be set at 50–60% of the complete occlusion pressure for the intervention group [35].

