#### 2.5.3. Exercise Protocol

All participants will perform biceps curls with a dumbbell from a standing position using BFR or sham BFR. The rhythm of the exercise will be paced using a metronome (60 bpm), and the biceps curls for each muscle contraction mode (concentric or eccentric) will last 2 s [41]. The initial resistance load will correspond to 5% of each participant’s body weight (±0.250 kg). Participants will be asked to perform 4 sets of bicep curls. The first set will consist of repetitions until failure (inability to follow the pace of the metronome, inability to complete the contraction on full range, or inability to perform an additional contraction), followed by 3 sets of 15 repetitions with a 30 s rest between the sets while the cuff remains inflated [25]. Therapists will encourage the participants to reach their maximum possible number of repetitions and inform them of the importance of completing all four sets. The participants’ inability to complete all set repetitions or to follow the pace of the metronome will indicate a resistance load reduction of 0.5 kg [42]. Immediately after the execution of the biceps curl exercise, the cuff will be deflated and removed for both groups.

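### Exclusion criterion 16 joins its two blood-pressure limits with *and*, so read literally one raised value alone does not exclude a volunteer from blood-flow-restriction exercise

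*Protocol article*

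**What the plan says.** Section 2.3 introduces its 20 numbered exclusions with "Participants will be excluded if they present any of the following criteria". Number 16 is hypertension, with the bracketed definition "systolic blood pressure greater than 140 mmHg and diastolic blood pressure greater than 90 mmHg". Number 12 is given only as "12) cardiovascular pathology", without a blood-pressure value.

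The exposure is described in three places:

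- The Introduction characterises the technique as "partial restriction of the arterial inflow and complete venous outflow restriction in the muscle tissue".
- Section 2.5.2 fixes the active dose: "The limb occlusion pressure will be set at 50–60% of the complete occlusion pressure for the intervention group".
- Section 2.5.3 prescribes four sets of biceps curls with the cuff kept inflated during the rests. Of these, "The first set will consist of repetitions until failure".

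The Abstract confirms the crossover: "The second session will involve participants switching treatment groups". Everyone who completes both sessions therefore receives the active restriction once.

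**The concern.** An exclusion labelled hypertension should remove people whose blood pressure is too high by the limits the protocol has chosen. With the two limits joined by *and*, the criterion removes only those who exceed both. Someone with an isolated systolic or an isolated diastolic elevation passes it, however large that one elevation is.

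What is at stake is safety at screening. The label indicates that the authors did not want hypertensive volunteers doing cuffed exercise, part of it to failure. The definition beneath the label can let some of them in. Two careful screeners could also decide differently on the same reading, one going by the label and the other by the thresholds. The wording does not touch the sample size, power or alpha.

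**Working it through.** The plan has no figure to reproduce here. The check is one of logic, applied to the printed limits.

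**Inputs (Section 2.3):** systolic limit 140 mmHg, diastolic limit 90 mmHg, both strict (greater than), joined by *and*.

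**Rule as printed:** exclude if (systolic > 140) AND (diastolic > 90).

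**Rule as proposed:** exclude if (systolic > 140) OR (diastolic > 90).

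The readings below are illustrations, not trial data.

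| Reading (mmHg) | Systolic > 140 | Diastolic > 90 | Printed rule | With *or* |
|---|---|---|---|---|
| 145/95 | yes | yes | excluded | excluded |
| 165/85 | yes | no | not excluded | excluded |
| 135/100 | no | yes | not excluded | excluded |
| 135/85 | no | no | not excluded | not excluded |

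The two rules differ only when exactly one value is above its limit.

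**Does anything else in the article close the gap?**

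- *The lead-in to the list.* It makes any one numbered criterion sufficient for exclusion. It works between criteria and does not change the conjunction inside number 16.
- *Criterion 12.* It could cover a volunteer with diagnosed cardiovascular disease. It sets no blood-pressure limit, so it gives no rule for an undiagnosed person with one raised screening value.
- *Section 2.5.2.* The pressure measured there is limb occlusion pressure. It is used to set the cuff and plays no part in eligibility.
- *Section 2.1, check before the second session.* It asks only whether the participant's clinical situation has changed.
- *Connectives elsewhere in Section 2.3.* Inclusion criterion 2 uses *and/or*, and exclusion criteria 2 and 15 use *or*. The section marks alternatives in other items, which gives a screener some reason to take the *and* in number 16 at face value.

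**Planned exposure.** Section 2.4 allocates 24 participants to each group. Active restriction is thus given to 24 in the first session and, after the switch, to at most 24 + 24 = 48. These are totals exposed, not counts of people affected by the wording.

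**The case against.** The strongest reply is that the label is the criterion and the bracket merely names one limit for each component of blood pressure. On that reading a screener who sees 165/85 under the heading of hypertension could reasonably exclude the volunteer. The list is loosely drafted elsewhere: rheumatic and neurological disease each appear twice, and the two surgery items overlap. The contrast with *and/or* in the inclusion criteria is therefore weak evidence that the *and* was chosen on purpose.

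The remaining gap is also narrow. Known hypertension is caught by the label and arguably by criterion 12, which leaves an undiagnosed volunteer with exactly one raised value, in a sample aged 18 to 40 with BMI below 30. The document does not say how hazardous a single raised reading is for this exercise, and it does not show the screening form. The comparison of active with sham restriction is made within the same participants, so the wording does not bias it.

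Most of this stands as a limit on the size of the problem. The intent may well have been *or*, the number affected may be small or zero, and no harm can be quantified. None of it changes what is printed. The bracket is the only operational definition of hypertension in the article, and a safety threshold should not depend on the screener guessing that *and* means *or*. Nor is this a detail left to a fuller document: the article states a specific rule with specific numbers.

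**Conclusion.** The concern holds. As printed, criterion 16 does not exclude a volunteer with exactly one blood-pressure value above its limit, and nothing else in the article supplies a rule that would. This is a participant-safety defect in an operative eligibility criterion and should be corrected. It is no threat to the trial's inference.

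The conclusion rests on reading the definition literally and on the inference, drawn from the label, that hypertensive volunteers were meant to be kept out. The number of participants affected is unknown, because the document gives no frequency of single raised readings in non-obese adults aged 18 to 40. The only bound available is the planned active exposure of up to 48.

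**What to change.** In criterion 16, replace *and* with *or*, so that a volunteer is excluded when systolic pressure is above 140 mmHg or diastolic pressure is above 90 mmHg. Leave both limits as they are. Make the same change on the screening form if it carries the same wording; the form is not shown.

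The cost is one word, plus possibly a few more screen failures. The age range and the exclusion of BMI 30 and above probably keep those few. The sample-size calculation and the analysis need no change.

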### 2.4. Randomisation and Blinding

Participants meeting the predetermined inclusion criteria will be randomly allocated to the BFR group (n = 24) or the sham BFR group (n = 24). For the randomisation of the participants, the “block randomisation” method will be applied through the randomisation website (http://www.randomization.com) by an external researcher, who will not have any contact with the participants throughout the study [27,36]. To ensure a balance in sample size between groups over time, we will randomise participants using a block randomisation method (blocks of 4). Random codes will be sealed in opaque envelopes and delivered to the physical therapist, who will undertake the intervention by an administrative assistant who will not be involved in the study [26].

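### The 20% dropout allowance is applied as 20 × 1.2, so 24 per group covers a loss of 16.7%; a minor slip with no material loss of power shown

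*Protocol article*

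**What the plan says.** Section 2.3 (Participants and Sample Size) of the protocol article builds the recruitment target in three steps.

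- Requirement: "To achieve 95% power at an alpha level of 0.05", the plan states that "20 patients per intervention for 3 assessment periods of outcome measures are required". The effect size comes from a previous study that "reported an effect size of d = 0.6 for differences in the NPRS between groups after the BFR exercise".
- Loss: 20%, because a participant's status may change between the two sessions.
- Target: "it is proposed to recruit 24 participants per group into the study, or 48 participants in total".

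The last two are joined as cause and result: "it is estimated that there will be a dropout of 20%, and thus, it is proposed to recruit 24 participants per group". Section 2.4 (Randomisation and Blinding) carries the target into the allocation, with participants "randomly allocated to the BFR group (n = 24) or the sham BFR group (n = 24").

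Section 2.1 sets the design: "This crossover design randomised controlled clinical trial will include two intervention arms (BFR and sham BFR) with three assessment time points". Participants switch intervention at the second session, so the two groups of 24 are sequence groups. Section 2.1 also says that anyone who reports a changed clinical situation is left out of the second session. That is the loss the allowance is meant to cover.

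**The concern.** An allowance for dropout should leave the required number after the stated loss. Here the required number was multiplied by one plus the rate. It should have been divided by one minus the rate. The first method always gives too small a target, because the loss falls on the larger recruited number and not on the required one.

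What is at stake is whether the recruitment figure does what the sentence says it does. The loss is one the plan expects to happen, since it follows from the plan's own check before the second session. The size of any consequence depends on what the 20 counts, and the section is not consistent about that: it is introduced per intervention, then treated as a number per group and doubled.

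**Working it through.** **Inputs**, all from section 2.3: requirement n = 20; loss d = 20% = 0.20; target 24 per group, 48 in total.

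**1. Reproducing the plan's figure.** n × (1 + d) = 20 × 1.2 = 24 per group, and 2 × 24 = 48. This matches exactly.

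**2. The allowance that a 20% loss needs.** n / (1 − d) = 20 / 0.8 = 25 per group, and 2 × 25 = 50.

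**3. What remains from the planned number at 20% loss.**
- Per sequence group: 24 × 0.8 = 19.2, about 19.
- Overall: 48 × 0.8 = 38.4, about 38.

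**4. The loss that 24 per group covers.** (24 − 20) / 24 = 4/24 = 16.7%. Overall, (48 − 40) / 48 = 8/48 = 16.7%.

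**5. Comparison with the requirement, on the two possible readings of 20.**

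| Reading of 20 | Completers needed | Completers at 20% loss | Difference |
|---|---|---|---|
| Per sequence group | 20 + 20 = 40 | about 38 | about 2 short |
| Receiving each intervention (20 people, each having both) | 20 | about 38 | about 18 over |

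**6. Effect on power (illustration only).** Section 2.3 gives neither the test, nor whether it is two-sided, nor a within-participant correlation, so both calculations below rest on assumptions.
- Per-sequence reading. Assume a two-sided paired t-test at α = 0.05 with a standardised within-participant difference of 0.6. It needs 39 participants for 95% power, close to 2 × 20. Power is 94.96% with 38 completers and 95.91% with 40, a difference of about one percentage point.
- In-total reading. Assume a one-group repeated-measures ANOVA with f = 0.6 / 2 = 0.3, six measurements (2 interventions × 3 times), a correlation of 0.5 and α = 0.05. It needs exactly 20 participants in total for 95% power (95.6% at 20), so 38 completers are well above the need.

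Each reading can thus be matched under some assumption, and the document does not settle which was used.

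**The case against.** The strongest reply is that the stated requirement is met. The text asks for 20 patients per intervention, and a total of 40 completers appears nowhere in it. The Discussion says that participants act as their own controls, so the roughly 38 who complete both sessions all receive BFR and all receive sham: 38 per intervention against 20. This stands as far as it goes, and it rules out saying flatly that the trial misses its required number. It does not rescue the arithmetic. The plan itself turns 20 per intervention into 24 per group and doubles it, which makes sense only if 20 is needed in each group, and on that reading the allowance is one short per group.

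A second reply is that those lost are not lost altogether. They are left out of session 2 only after session 1 has been measured at all three time points, and the mixed-effects models of section 2.7 have participant random effects and no stated restriction to completers. Their session 1 data can be used. This also stands, and it softens the effect further.

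A reader might infer that the trial is underpowered. The documents do not support that. Under the paired illustration, power with 38 completers is 94.96%, which is the stated 95% to rounding; under the repeated-measures illustration there is a surplus.

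**Conclusion.** The concern holds as a minor correction. The 20% allowance is wrong as written: 24 per group covers a loss of 16.7%, and a 20% loss would take 25. This part rests on nothing outside section 2.3.

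The shortfall of one per sequence group, about two overall, is conditional on 20 completers being required in each sequence. If 20 is the number receiving each intervention, there is none. No material loss of power is shown on either reading, and no analysis or conclusion changes. The power figures are illustrations under assumed tests and should not be read as the plan's own. In particular, the plan quotes d = 0.6 as a difference between groups, which cannot be taken as a paired effect size without a correlation.

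**What to change.** Keep 48 and restate the sentence in section 2.3, for example:

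> 48 participants (24 per sequence) will be randomised. This allows for a 16.7% loss if 20 completers per sequence are required. With the anticipated 20% loss, about 38 participants will complete both sessions.

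In the same edit, say whether the 20 is per sequence or in total; if it is in total, drop the conditional sentence on 16.7%. Do not attach a power figure for a paired effect of 0.6 unless the test and the within-participant correlation are stated with it.

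The cost is a sentence or two: no more patients, no change to design or allocation. Raising the target to 50 is the alternative, but 50 is not a multiple of the block size of 4 in section 2.4 and would go up to 52; the size of the effect does not call for it.
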